## Abstract

**Introduction:** Brain edema after acute intracerebral hemorrhage (ICH) plays a critical role in the secondary injury of ICH and may heighten the potential for a poor outcome. This trial aims to explore the efficacy of small doses of oral glibenclamide in perihematomal edema (PHE) and the prognosis of patients with ICH.

**Methods and Analysis:** The GATE-ICH trial is a multicenter randomized, controlled, assessor-blinded trial. A total of 220 adult patients with acute primary ICH in 28 study centers in China will be randomized to the glibenclamide group (glibenclamide plus guideline-recommended ICH management) or the control group (guideline-recommended ICH management). Multivariate logistic regression will be used to analyze the relationship between the treatments and primary outcome.

**Study Outcomes:** The primary efficacy outcome is the proportion of poor functional outcomes (modified Rankin Scale ≥3) at 90 days after enrollment. The secondary efficacy outcomes include changes in the volume of ICH and PHE between the baseline and follow-up computed tomography scans as well as the clinical scores between the baseline and follow-up assessments.

**Discussion:** The GATE-ICH trial will assess the effects of small doses of oral glibenclamide in reducing the PHE after ICH and improving the 90-day prognosis of patients.

**Clinical Trial Registration:**
www.clinicaltrials.gov., NCT03741530. Registered on November 8, 2018.

**Trial Status:** Protocol version: May 6, 2019, Version 5. Recruitment and follow-up of patients is currently ongoing. This trial will be end in the second quarter of 2021.

## Introduction

Intracerebral hemorrhage (ICH) accounts for 10–15% of the 15 million strokes worldwide each year and has a high mortality and morbidity (1). Compared with Western populations, the incidence of ICH in the Chinese population is higher (1, 2). However, only 12–39% of ICH survivors achieve long-term functional independence (3, 4). Despite the severe outcomes, there are no effective medical or surgical therapeutics available (5).

Perihematomal edema (PHE) after primary ICH, as a combination of early vasogenic edema following cytotoxic edema (6, 7). It is the most critical factor of secondary brain injury that leads to additional neurological deterioration (8, 9). The volume of PHE increases by ~75% during the first 24 h after ICH. It peaks in ~5–6 days, and continues for 14 days (1). Managing PHE may be an optimal target for ameliorating secondary brain injury in patients with ICH (10).

Most recently, glibenclamide, a sulfonylurea (SFU) drug and potent inhibitor of the sulfonylurea receptor 1-transient receptor potential melastatin 4 (SUR1-TRPM4) channels, has attracted great interest as a promising therapy for the prevention of cerebral edema after hemispheric infarction. It has been verified in the GAMES-RP study (11–13). Glibenclamide may contribute to mitigating both cytotoxic and vasogenic edema by blocking the SUR1-TRPM4 channels, inhibiting apoptosis, scavenging free radicals, and protecting the integrity of the blood-brain barrier (BBB) (14–16). In patients with ICH with a history of diabetes, SFU used prior to ICH could reduce the accumulation of ICH and PHE volume and improve the short-term prognosis (17, 18). Given the safety and efficacy of oral glibenclamide in treating edema after brain injury, we supposed that the oral formulation of glibenclamide would be efficacious in preventing PHE in patients with acute ICH.

## Methods and Analysis

### Study Objectives

The purpose of this hospital-based study is to assess whether small doses of oral glibenclamide would reduce edema and improve the prognosis in patients with ICH.

### Study Design

The Glibenclamide Advantage in Treating Edema after Intracerebral Hemorrhage (GATE-ICH) study is a multicenter, randomized, controlled, assessor-blinded clinical trial. The subjects will be randomized into one of the two intervention arms using a web-based 1:1 centralized randomization process (http://cerebralhemorrhage.applinzi.com. computerized random numbers): (1) the glibenclamide group (glibenclamide plus guideline-recommended ICH management), and (2) the control group (guideline-recommended ICH management). There are four time points of assessment: baseline (t0), 3 days (t1), 7 days (t2), and 90 days (t3) after enrollment (Table 1). The Supplementary File 1 describes the Recommendations of Interventional Trials (SPIRIT), which indicates the recommended items and corresponding page numbers of the present protocol.

**Table 1 T1:** Overview of assessment points and measurements.

**Assessment points**	**Time range**
t0	baseline assessment prior to enrollment
t1	3 days (72 h ± 12 h) post-enrollment
t2	7 days (168 h ± 12 h) post-enrollment
t3	90 days (± 7 d) post-enrollment

### Study Population

The GATE-ICH trial (www.clinicaltrials.gov. NCT03741530) involves 26 hospitals in the Shaanxi Province of China. We will conduct the study based on the recommendations of the Good Clinical Practice guidelines and the Declaration of Helsinki. The trial has been approved by the ethics committee of Xijing Hospital (KY20182067-X-3). The study will include patients with acute primary ICH who have ganglia hemorrhage of 5–30 mL confirmed by a baseline head computed tomography (CT). The inclusion criteria and exclusion criteria are shown in Box 1. Potential patients will be identified by emergency physicians and the initial neurologists. Trained neurologists at every center will be requested to make a definite diagnosis of ICH and confirm that each patient has met the inclusion criteria of the study. A written informed consent form of the present study and additional *post-hoc* analysis will be sent to all of the subjects or their guardians by the trained neurologists.

Box 1Inclusion and exclusion criteria.**Inclusion criteria**Age 18–70 years with primary ICH.Baseline CT with basal ganglia hemorrhage of 5–30 mL.GCS score ≥ 6.Symptom onset <72 h prior to admission.Informed consent.**Exclusion criteria**Supratentorial ICH planned to evacuation of a large hematoma.Hemorrhage breaking into ventricles of the brain.Prior significant disability (mRS ≥ 3).Severe renal disease (i.e., renal disorder requiring dialysis) or eGFR <30 ml/min/1.73 m^2^.Severe liver disorder, or ALT >3 times or bilirubin >2 times upper limit of normal.BG <3.1 mmol/L at enrollment, or with the history of hypoglycemia.Having acute ST elevation infarction, or decompensated heart failure, or cardiac arrest, or acute coronary syndrome, or known history of acute coronary syndrome, or acute myocardial infarction, or coronary intervention in the past 3 months.Treatment with sulfonylurea in the past 7 days, including glyburide, glyburide plus metformin, glimepiride, repaglinide, glipizide, gliclazide, tolbutamide, and/or glibornuride.Treatment with bosentan in the past 7 days.Having an allergy to sulfa or other sulfonylurea drugs.Known G6PD deficiency.Pregnant women.Breast-feeding women disagreeing to participate the study or to discontinue breastfeeding during and after the study.Being enrolled in another study and receiving an investigational drug.Refusing to be enrolled, having poor compliance, and/or tending to withdraw.ALT, Alanine aminotransferase; BG, Blood glucose; CT, computed tomography; eGFR, estimated glomerular filtration rate; GCS, Glasgow Coma Scale; G6PD, Glucose-6-phosphate Dehydrogenase; ICH, intracerebral hemorrhage; mRS, modified Rankin Scale.

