### Trial Interventions

#### Intervention Arms

The time course of plasma glibenclamide levels indicates that an oral formulation of 3.5 mg/day at 4 h after administration is equal to an intravenous formulation of a 0.13-mg bolus followed by a dose of 3 mg/day, which has been proved efficacious and safe for treating edema in patients with ischemic stroke (13, 19). The half-life of glibenclamide is 4.0–13.4 h in elderly patients and 4.0–13.9 h in younger patients (20). In order to achieve a stable drug concentration that coincides with three mealtimes, we chose a dose of 1.25 mg, 3 times per day (3.75 mg/day). In our pilot study, 10 patients in the glibenclamide group and 12 patients in the control group were enrolled. The plasma concentration of glibenclamide elevated to 47.6 ng/mL at 2 h after the first dose, and gradually achieved by steady state plasma concentration of glibenclamide at 72 h (26.7 ng/mL). Patients assigned to the glibenclamide group will receive tablets containing 1.25 mg of glibenclamide [Yun Peng Pharmaceutical Co., Shanxi, China; each capsule (2.5 mg)] three times daily (no more than 30 min before a meal) for 7 consecutive days after enrollment in addition to the usual care and medications for ICH. Patients in the control group will receive only the usual care and medications for ICH. Glibenclamide tablets should not be administered after head CT on day 7. Treatment with other SFU agents is not permitted during the 90-day follow-up period in either group.

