### Study Procedures

Figure 1 presents the flow chart of the GATE-ICH trial. Based on the inclusion and exclusion criteria, the potential subjects offering informed consent will be randomized. At baseline, demographics, medical history (acute ischemic stroke, ICH, coronary events, diabetes mellitus, and hypertension), physical examination results, clinical scores (NIHSS, GCS, ICH score, Barthel index, mRS), vital signs, and head CT results will be recorded. Routine laboratory tests for patients with ICH will be conducted (routine blood tests, renal and liver function tests, serum lipid, fasting glucose, routine urine tests, electrocardiography, and head CT) on days 1, 3, and 7. Clinical scores (NIHSS, GCS, Barthel index, and mRS) on day 3 and day 7 or the day of hospital discharge will be collected. The Barthel index and mRS on day 90 will be assessed. During the entire period of hospitalization, concomitant treatments, adverse events (AEs), and serious AEs (SAEs) will be documented.

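### The 72-hour limit runs from onset to admission while dosing and follow-up CTs run from enrollment, so time from onset has no stated limit and the edema-change endpoint carries avoidable variance

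*Protocol article*

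**What the plan says.** The protocol article uses two clocks.

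- **Eligibility** (Study Population, Box 1) counts from onset to hospital admission: "Symptom onset <72 h prior to admission".
- **Treatment** (Intervention Arms) counts from enrollment: tablets are given "for 7 consecutive days after enrollment".
- **Assessments** (Study Design, Table 1) also count from enrollment: t1 is "3 days (72 h ± 12 h) post-enrollment" and t2 is "7 days (168 h ± 12 h) post-enrollment". Baseline, t0, is only a "baseline assessment prior to enrollment".

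No section states a maximum time from admission to enrollment, from onset to baseline CT, or from onset to first dose.

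The Introduction describes edema on a third clock, time since the hemorrhage: "The volume of PHE increases by ~75% during the first 24 h after ICH", and then "It peaks in ~5–6 days, and continues for 14 days".

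Study Outcomes lists the change in PHE volume from baseline to follow-up CT as a secondary efficacy endpoint. Statistical Considerations compares continuous outcomes by t-test or Wilcoxon rank-sum test. The only adjusted analysis it describes is a logistic model with unnamed covariates.

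**The concern.** A change score means the same thing in every patient only if its start and end points fall at comparable stages of the process. Here the process is tied to onset and the schedule to enrollment, and the link between the two is left open.

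A patient scanned at hour 3 has a baseline before most of the first-day growth that the Introduction describes. A patient scanned at hour 70 has a baseline after it. Subtracting each baseline from a day-7 volume gives two different quantities under one name. The difference between patients enters the unadjusted comparison as residual variance. With about 110 patients per arm (220 / 2), some chance imbalance in onset time is also possible.

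What is at stake is the precision and the reading of the imaging endpoint that carries the trial's mechanistic hypothesis.

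**Working it through.** The plan gives no figure of its own for time from onset, so there is none to reproduce. The check is interval arithmetic.

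**Inputs**
- Onset to admission: 0 to 72 h (Box 1).
- Admission to enrollment: 0 to D h. D is not stated, so I assume 0, 24, 48 and 72 h to show the range.
- t1: 72 − 12 = 60 h to 72 + 12 = 84 h after enrollment (Table 1).
- t2: 168 − 12 = 156 h to 168 + 12 = 180 h after enrollment (Table 1).
- Stated edema peak: days 5–6, that is 120–144 h after onset (Introduction).

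**Formulas**
- Latest enrollment after onset = 72 + D.
- Earliest t1 = 0 + 60; latest t1 = 72 + D + 84.
- Earliest t2 = 0 + 156; latest t2 = 72 + D + 180.

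**Results, hours (days) after onset**

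| Assumed maximum D | Enrollment | t1 CT | t2 CT |
|---|---|---|---|
| 0 h | 0–72 (0–3.0) | 60–156 (2.5–6.5) | 156–252 (6.5–10.5) |
| 24 h | 0–96 (0–4.0) | 60–180 (2.5–7.5) | 156–276 (6.5–11.5) |
| 48 h | 0–120 (0–5.0) | 60–204 (2.5–8.5) | 156–300 (6.5–12.5) |
| 72 h | 0–144 (0–6.0) | 60–228 (2.5–9.5) | 156–324 (6.5–13.5) |

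**What follows**
1. With D = 0 the spread at each follow-up CT is 96 h (156 − 60 and 252 − 156). That is the 72 h entry window plus the 24 h visit window.
2. If the same 72 h were counted to randomisation, the first row would be the whole answer. Re-anchoring therefore removes only the rows below it. It does not reduce the 96 h.
3. The earliest t2 CT is at 6.5 days, after the stated 5–6 day peak. So every day-7 CT lies past the peak, and variation in phase for baseline-to-day-7 change comes mainly from the baseline scan. The t1 CT does straddle the peak (2.5 to 6.5 days even with D = 0).
4. Because baseline need only precede enrollment, the length of the change interval also varies. If baseline is B hours before enrollment, baseline to t2 lasts 156 + B to 180 + B hours, and B has no stated limit.
5. An enrollment, and so potentially a baseline CT, at the stated peak requires D of at least 48 h (72 + 48 = 120 h) for a patient admitted at the limit of the window. Nothing in the text excludes this, and nothing says how often it would occur.

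The loss of precision in PHE change cannot be computed, because the article gives no distribution of onset times and no volume-by-time data.

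**The case against.** Five points can be made for the plan as written.

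- **The only firm spread is not caused by the anchor.** A reader might blame the admission anchor for the 6.5 to 10.5 days. That is wrong: the range assumes no delay and reflects the width of the window. This stands.
- **Long delays are assumed, not documented.** The article speaks of acute hemorrhage, with candidates identified by emergency physicians and the initial neurologists, so delays may well be short. This stands as to practice. It does not supply a limit in the text.
- **Late entrants may still benefit.** A reader might infer that they have little preventable edema and so dilute the mRS result. The documents do not show it: a patient enrolled at 72 h is still two to three days short of the stated peak, with seven days of treatment ahead.
- **There is no systematic bias.** Central 1:1 randomisation balances onset time in expectation, and both arms share the same scan windows. This stands.
- **Covariates may be named in an analysis plan that is not shown.** For the logistic model this is fair, and its unnamed covariates are not criticised here. For continuous outcomes, however, the article does name its tests, and they are unadjusted.

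**Conclusion.** The point holds in a limited form. The eligibility clock stops at admission while the treatment and follow-up clocks start at enrollment. As written, time from onset to randomisation, first dose and CT is therefore not bounded. Since the article itself describes edema by time since hemorrhage, the baseline CT can sit at very different stages, and an unadjusted comparison of PHE change leaves that variation in the error term.

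The consequence is reduced precision and interpretability of a secondary endpoint. Two stronger readings are not supported: that the treatment comparison is biased, and that the primary mRS effect is diluted. An mRS effect through time to treatment is possible but not shown.

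On size, the 96 h spread at each follow-up CT is certain as a permitted range and comes from the 72 h width. The further spread from in-hospital delay rests on an assumed D and cannot be quantified from the article. The cost of correction is low, so this is a worthwhile improvement, not a defect that threatens the trial's main conclusion.

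**What to change.** 1. **Analysis.** Replace the unadjusted comparison of PHE change with a regression (ANCOVA) of follow-up change on treatment, adjusted for baseline PHE volume, time from onset to baseline CT and time from onset to the follow-up CT. Prespecify it before the blinded analysts learn the allocation. This is the part that addresses the mix of edema phases, and it can cover patients already enrolled wherever the times are available. Onset time has to be obtained anyway to apply Box 1, so the added cost is little more than making sure the CT times are available.

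2. **Anchor.** For patients still to be enrolled, reconcile the two clocks by counting the existing 72 h from onset to randomisation. The length of the window is not questioned here; only its end point changes. This closes the open-ended interval but leaves the 96 h spread, so it does not replace step 1.

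The second step has a cost. Recruitment is ongoing, and Protocol Amendments requires agreement from the study group, sponsor and funder, then ethics approval and notice to investigators and the registry. The criterion would differ slightly between earlier and later entrants, and the few patients randomised after 72 h would be lost.

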### Randomization

The baseline data of potential participants will be provided to the research coordinators by investigators at every center. Through a web-based 1:1 randomization (computerized random numbers) process (http://cerebralhemorrhage.applinzi.com/index.php), patients will be assigned to one of the two intervention arms by the research coordinators.

### Training of Investigators

To ensure the quality of the GATE-ICH trial, all the investigators from every center are required to receive official training regarding the study protocol, Good Clinical Practice guidelines, clinical scores including the Glasgow Coma Scale (GCS), National Institutes of Health Stroke Scale (NIHSS), ICH score, Barthel index, and modified Rankin Scale (mRS), as well as the recognition of basal ganglia hemorrhage on head CT.

### Trial Interventions

#### Intervention Arms

The time course of plasma glibenclamide levels indicates that an oral formulation of 3.5 mg/day at 4 h after administration is equal to an intravenous formulation of a 0.13-mg bolus followed by a dose of 3 mg/day, which has been proved efficacious and safe for treating edema in patients with ischemic stroke (13, 19). The half-life of glibenclamide is 4.0–13.4 h in elderly patients and 4.0–13.9 h in younger patients (20). In order to achieve a stable drug concentration that coincides with three mealtimes, we chose a dose of 1.25 mg, 3 times per day (3.75 mg/day). In our pilot study, 10 patients in the glibenclamide group and 12 patients in the control group were enrolled. The plasma concentration of glibenclamide elevated to 47.6 ng/mL at 2 h after the first dose, and gradually achieved by steady state plasma concentration of glibenclamide at 72 h (26.7 ng/mL). Patients assigned to the glibenclamide group will receive tablets containing 1.25 mg of glibenclamide [Yun Peng Pharmaceutical Co., Shanxi, China; each capsule (2.5 mg)] three times daily (no more than 30 min before a meal) for 7 consecutive days after enrollment in addition to the usual care and medications for ICH. Patients in the control group will receive only the usual care and medications for ICH. Glibenclamide tablets should not be administered after head CT on day 7. Treatment with other SFU agents is not permitted during the 90-day follow-up period in either group.

#### Patient Safety

The study drug must be reduced to 1.25 mg twice daily if any of the following conditions are present: (1) laboratory-confirmed blood glucose (BG) level <3.1 mmol/L; (2) or three laboratory-confirmed BG levels <3.9 mmol/L within 12 h. The study drug must be discontinued if either of these conditions occur twice. In patients with hyperglycemia during their hospitalization, increasing the dosage of glibenclamide or substituting glibenclamide with other SFU agents is not permitted. In patients with a laboratory-confirmed BG level <3.9 mmol/L, administration of 50% glucose is suggested, according to the following formula: supplementation volume of 50% glucose = [100–laboratory-confirmed BG (mg/dL)] × 0.4 mL. Other highly hyperosmotic glucose solutions with the same amount of sugar are also allowed.

#### Medical Care in the Hospital

Both groups in the present study will receive the same background care. Traditional dehydration therapy is not recommended for patients without intracranial hypertension. In patients with intracranial hypertension, the selection of osmotherapy medicines depends on local availability. The use of supplemental fluids is based on the clinical status of the subjects. In patients randomized to the glibenclamide group with inadequate intake, but not meeting the standard nasal feeding, 5 or 10% glucose is recommended to avoid hypoglycemia. The management of blood pressure and all other medical care for ICH patients will adhere to the ICH guidelines (21).

### Study Procedures

Figure 1 presents the flow chart of the GATE-ICH trial. Based on the inclusion and exclusion criteria, the potential subjects offering informed consent will be randomized. At baseline, demographics, medical history (acute ischemic stroke, ICH, coronary events, diabetes mellitus, and hypertension), physical examination results, clinical scores (NIHSS, GCS, ICH score, Barthel index, mRS), vital signs, and head CT results will be recorded. Routine laboratory tests for patients with ICH will be conducted (routine blood tests, renal and liver function tests, serum lipid, fasting glucose, routine urine tests, electrocardiography, and head CT) on days 1, 3, and 7. Clinical scores (NIHSS, GCS, Barthel index, and mRS) on day 3 and day 7 or the day of hospital discharge will be collected. The Barthel index and mRS on day 90 will be assessed. During the entire period of hospitalization, concomitant treatments, adverse events (AEs), and serious AEs (SAEs) will be documented.

**Figure 1 F1:**
[figure not shown]
Flowchart of the trial design.

#### Imaging Evaluations

A baseline CT evaluation of ICH volume will be performed by the investigators and study coordinators in each center using an image matrix of 512 × 512 with a slice thickness of 5 mm. The three CT assessments of the same subject should use the same type of CT. At an initial meeting, all investigators will be trained on the methodology of hematoma volume calculation using ABC/2 and provided with an electronic instruction manual. CT scans will be performed as standard procedures, and additional magnetic resonance imaging or other scans will be used when patients appear to have neurological deterioration. The final results of the three CT scans in every patient will be evaluated by independent investigators blinded to the clinical variables using the 3D Slicer software package (version 4.10.2; National Institutes of Health, Bethesda, MD, USA). ICH and PHE volumes will be measured using a semiautomatic volumetric algorithm as in a previous study (Figure 2) (22, 23).

